### Randomization

After signing the informed consent form for study participation and completion of the baseline questionnaire, randomization will be performed by the study leader ([name]) or a research assistant using Castor EDC (https://www.castoredc.com), a Good Clinical Practice (GCP-)approved online tool, to divide cancer survivors in either the STEPS intervention or usual care control group. Variable block randomization will be applied with stratification per recruiting hospital. In Castor EDC, allocation sequence is concealed. However, due to the nature of the intervention, neither cancer survivors nor those who deliver the intervention or analyse the results will be blinded to the randomization. All cancer survivors randomized to one of the two trial arms will be considered to be included in the study, and will thus be followed during the follow-up period.

### STEPS intervention

STEPS is a multidisciplinary intervention based on the Stages of Change, and combines work-related occupational therapy and reintegration consultation, to support cancer survivors in their RTW and work retention. The STEPS intervention program was designed both bottom-up (i.e., theory-driven, using the Stages of Change model [11]) and top-down (i.e., by interviews with experts and cancer survivors, as described in more detail elsewhere ([name], [name], [name], [name], [name], [name]. Tailoring work participation support for cancer survivors using the Readiness for Return to Work scale: perspectives and opinions of (health care) professionals and cancer survivors. In preparation.)). The intervention will be delivered by both occupational therapists and reintegration consultants, who tailor the intervention content according to the Stages of Change as measured by the RRTW. Occupational therapists are working at the outpatient clinics of participating hospitals. Most occupational therapists involved in the delivery of STEPS have experience with work-related guidance of cancer survivors. Those who do not, have experience with providing other aspects of occupational therapy to cancer survivors. All involved occupational therapists received a half day STEPS intervention training and will participate in peer intervision sessions throughout the intervention period. Involved reintegration consultants in STEPS are employed at a private reintegration consultancy, specialized and experienced in work-related support of cancer survivors. Reintegration consultants were trained in the STEPS intervention content as well. The content of the STEPS intervention has been described in the 89-page STEPS intervention handbook (in Dutch, available in PDF upon request). The intervention was designed to be delivered face-to-face, but will also be available remotely (i.e., using video conferencing or telephone meetings) if necessary (e.g., in case of COVID-19 regulations).

See Fig. 2 for a logic model of the STEPS intervention elements, and Supplementary file 2 for an overview of the intervention components per behavioural change stage. The STEPS intervention has a maximum duration of 6 months, during which cancer survivors receive a minimum of three and a maximum of nine sessions, depending on their work-related support needs. STEPS is aimed at supporting cancer survivors’ work-related self-efficacy during their RTW or work retention process, and to encourage them to develop and maintain effective communication with their employer. During the STEPS intervention, the cancer survivors’ behavioural change stage will be monitored continuously and the intervention will be tailored to the specific stage the survivor is in. To do so, cancer survivors will be asked to complete a brief questionnaire (i.e., a Dutch version [25] of the Readiness for Return To Work - RRTW [15]) and an abbreviated version of the Return to Work Obstacles and Self-Efficacy Scale - ROSES [26]) prior to each session with the occupational therapist. Based on the outcomes of the RRTW questionnaire, participants will be categorised according to one of the six stages of change (pre-contemplation, contemplation, preparation: self-evaluative, preparation: behavioural, uncertain and proactive maintenance). Within each of these stages, participants will furthermore be given a traffic light designation (i.e. red, orange or green), based on the outcomes of the ROSES questionnaire, depicting potential barriers and facilitators regarding sustained employment and their overall progress within the intervention. Based on this categorisation the occupational therapist can, using the STEPS handbook, tailor the intervention provided (see Supplementary File 2).

**Fig. 2 Fig2:**
[figure not shown]
Logic model of the STEPS intervention elements, expected changes and outcomes

The intervention includes the following elements:
Introductory session (1.5 h duration) that will take place with the occupational therapist and the cancer survivor. The session is aimed at clarifying the cancer survivor’s work-related circumstances, expectations, and support needs, including barriers and facilitators for RTW or work retention (i.e., using the RRTW [15]) and ROSES [26] questionnaires), setting work-related goals, and co-developing a plan for the upcoming sessions.A minimum of one and a maximum of six one-on-one sessions (1 h duration each) with the occupational therapist and the cancer survivor. These sessions are aimed at preparing the cancer survivor for RTW or work retention, using psycho-education, energy management, self-efficacy training, facilitating contact with their employer and occupational physician, and developing and trying out a RTW/work retention plan.A minimum of one and a maximum of two sessions (1.5 h duration each) with the reintegration consultant and the cancer survivor. These sessions are aimed at providing information regarding the relevant legal framework in the Netherlands, effective communication about reintegration with/after cancer, RTW planning, or the long-term effects of cancer (treatment) on work. These information sessions can take place one-on-one, or together with a relevant person from the cancer survivor’s workplace (e.g., direct supervisor or human resource officer).

### Care as usual

Participants in the control group will receive usual care regarding sustained employment, the content and availability of which will vary per participating hospital. In the Netherlands, there is no structured provision of work-related care for cancer survivors in hospitals, and we have shown before that the extent to which such care is provided to cancer survivors is therefore limited [4]. Nonetheless, work-related care is sometimes delivered as part of the care provided by various health care providers including occupational therapists, social workers, rehabilitation care practitioners or physiotherapists.

### Measurements

Baseline and follow-up questionnaires for both the RCT and cohort study will be digitally administered using Castor EDC (https://www.castoredc.com). Questionnaires can be accessed through a link that will be sent via e-mail. Participants who have expressed a preference for hardcopy versions of the questionnaires will receive them at their home address. Participants will receive one reminder for each questionnaire, 2 weeks after the questionnaire has been sent. If participants do not return the six-month follow-up questionnaire, and unless they have withdrawn their participation from the study, they will receive the 12-month follow-up questionnaire. Table 1 provides an overview of all measurements incorporated in the questionnaires (primary and secondary outcomes and additional measurements; for cancer survivors and partners). Table 2 shows how all constructs will be operationalized, measured, and processed for further analyses, including references to individual questionnaires.

**Table 1 Tab1:** Overview of variables that will be measured in the STEPS randomized controlled trial (RCT) among cancer survivors and the cohort study among partners of cancer survivors

Category	Variable	RCT among cancer survivors				Cohort study among partners of cancer survivors			
		T0 (Baseline)	T1 (6-month)	T2 (12-month)	Variable^a^	T0 (Baseline)	T1 (6-month)	T2 (12-month)	Variable^a^
Work outcomes	Working hours per week	X	X	X	P	X	X	X	P
	Change in working hours (%)	X	X	X	S	X	X	X	S
	Employment status	X	X	X	S	X	X	X	S
	Time to return to work	X	X	X	S^b^				–
	Sick leave	X	X	X	S	X	X	X	S
	Readiness for return to work	X	X	X	S				–
	Work ability	X	X	X	S				A
Health outcomes	Health-related work functioning	X	X	X	S^c^	X	X	X	S
	Health-related quality of life	X	X	X	S	X	X	X	P
	Caregiver burden				–	X	X	X	S
	Depression	X			A	X	X	X	S
Sociodemographic	Age, gender	X			A, M	X	X		A
	Marital status	X			A	X	X		A
	Children living at home	X			A	X	X		A
	Education and income	X			A	X	X		A
	Breadwinner status	X			A	X	X		A
Medical	Cancer site	X			A, M	X	X		A^d^
	Time of diagnosis	X			A, M	X	X		A^d^
	Received and future treatment(s)	X			A, M	X	X		A^d^
	Cancer recurrence(s)	X			A	X	X		A^d^
Lifestyle	Smoking	X			A	X	X		A
	Alcohol consumption	X			A	X	X		A
	Physical activity	X			A	X	X		A
Health	Comorbidities	X			A	X	X		A
	Fatigue	X			A	X	X		A
Employment	Main tasks	X			A	X	X		A
	Years in current position	X			A	X	X		A
	Years of paid employment (and in current job)	X			A	X	X		A
	Contract type (fixed/temporary)	X			A	X	X		A
	Shift work	X			A	X	X		A
	Company size and sector	X			A	X	X		A
	Time since first day of sick leave	X			A				–
	Employment status partner (if applicable)	X			A				–
	(duration of) Caregiving leave				–	X	X		A
Work	Social support from supervisor/colleagues	X			A	X	X		A
	Job insecurity	X			A	X	X		A
	Need for recovery	X			A^c^	X	X		A
	Work accommodation	X			A^c^	X	X		A
	Impact of COVID-19 on work	X			A^c^	X	X		A
	Work attitude	X			A	X	X		A
	Self-efficacy	X			A	X	X		A
	Work-family balance	X			A^c^	X	X		A
	Work intention	X			A	X	X		A
	Fear of COVID-19	X			A	X	X		A
	Expectations regarding return to work	X			A				–
Process measures			X		P				–
Economic evaluation	Quality of life	X	X	X	E				–
	Health care consumption	X	X	X	E				
	Productivity loss	X	X	X	E				

^a^*P* Primary outcome variable, *S* Secondary outcome variable, *A* Additional variable, *M* Modifier, *E* Economic evaluation variables, *P* Process variables

^b^Only completed by participants who were on sick leave at baseline

^c^Only completed by participants who (partly) returned to work

^d^The partner will be asked regarding the medical status of the cancer survivor

**Table 2 Tab2:** List of primary, secondary and additional variables and their assessment methods

		Instrument	# items	Rating scale	Operationalization
Work outcomes	Working hours per week	Asking participants for their current number of actual working hours	1	n/a	Continuous
	Change in working hours (%)	Asking participants for their current number of actual working hours and their contractual working hours at baseline.	1	n/a	Continuous (actual working hours at follow-up as a percentage of contractual working hours at baseline).
	Employment status	Asking participants whether they are at work or not at work	1	n/a	Dichotomous
	Time to return to work	Asking participants about their first day of returning to work, from which we will estimate the number of calendar days between the first day of sick leave and the first day of work, either fulltime or part-time, for at least 28 consecutive days without recurrence.	1	n/a	Continuous
	Sick leave	Asking participants about the number of days they have been on sick leave in the past 6 months	1	n/a	Continuous
	Readiness for return to work	The translated and adapted Dutch version [25] of the original RRTW questionnaire [15]. There are a number of items for each of the phases, with each item being scored on a 1 to 5 scale. Each RRTW stage will be scored by averaging all items within that stage. The stage with the highest summary score was considered the stage the participant was in. In case of a tie between stages, the lowest RRTW stage will be adopted. Based on this participants will be classified in any of the six RRTW phases.	21	6 stages	Ordinal
	Work ability	Single question of the Work Ability Index (WAI) [27], asking participants to estimate their current work ability compared with their lifetime best on 0 to 10 scale (0 = cannot work at all; 10 = best ever);	1	10-point scale	Continuous
Health outcomes	Health-related work functioning	The validated [28] 27-item Work Role Functioning Questionnaire (WRFQ) [29], distinguishing five different work domains: work scheduling demands, mental demands, social demands, physical demands, and output demands (range 0 to 100). Higher scores indicate better work functioning.	27	0 to 100	Continuous
	Health-related quality of life	For patients: the European Organization for Research and Treatment of Cancer Quality of Life Questionnaire – Core 30 (EORTC QLQ C-30) [30]). This 30-item list consists of five multi-item functional scales (i.e., physical, role, emotional, cognitive, and social), three multi-item symptom scales (i.e., fatigue, pain, and nausea and vomiting), six single-item (i.e., dyspnoea, insomnia, appetite loss, constipation, diarrhoea, and financial impact), and a two-item global health and quality of life scale, all with a scoring range from 0 to 100. A higher score on the functional and global health and quality of life scales indicates better quality of life, while on the symptom scales, a higher score indicates a higher level of symptom burden. A summary score will be generated, calculated as the mean of all combined scale scores, excluding financial impact and the global health and quality of life scale.	30	0 to 100	Continuous
		For partners: 12-item short-form health survey (SF-12) [31], expressed in t-score.	12	n/a	Continuous
	Caregiver burden	The ‘Ervaren Druk door Informele Zorg-plus’ (EDIZ) [32], consisting of 15 items, ranging from 0 to 1, higher scores indicate a higher caregiver burden	15	0 to 15	Continuous
	Depression	The Centre for Epidemiological Studies Depression Scale [33];, consisting of 20 items and a range of 0 to 60, a score of 16 and over indicates the possible presence of clinical depression	20	0 to 60	Dichotomous
Sociodemographic	Age	Asking participants about their age (in years)	1	n/a	Continuous
	Gender	Asking participants about their gender (male/female)	1	n/a	Dichotomous
	Marital status	Asking participants about their marital status with answer options: Not married, married without children, married with children, living together with partner, living together with partner and children, living together with others, single with children, divorced, widow/widower.	1	n/a	Categorical
	Children	Number of children (living at home)	2	n/a	Continuous
	Education	Asking participants about their highest education level completed with eight outcome options according to the Dutch education system.	1	n/a	Categorized in low, middle, high (according to International Standard Classification of Education (ISCED-97).
	Income	Asking participants about their annual income (before tax) with answer options: <€30.000, €30.000–€60.000, €60.000–€100.000, and > €100.000.	1	n/a	Categorical
	Breadwinner status	Asking participants about their breadwinner status with answer options: being sole breadwinner, not being breadwinner, being shared breadwinner with partner, don’t know	1	n/a	Categorical
	Financial necessity of work	Asking about financial necessity of work	1	n/	Dichotomous
Medical	Cancer site*	Asking participants about their cancer site with 17 answer options (being the most common cancer sites) and the answer option ‘other’	1	n/a	Categorical
	Time of diagnosis*	Asking participants for their time of diagnosis, which can be calculated in the time since diagnosis.	1	n/a	Continuous
	Treatment(s)*	Received and future treatment(s). E.g. surgery, radiation, chemotherapy, hormonal therapy, or combination, and medication	1	n/a	Categorical
	Cancer recurrence(s)*	Asking about recurrence of cancer in the follow-up questionnaires.	1	n/a	Dichotomous
Lifestyle	Smoking	Asking participants about their smoking status with answer options: smoker, ex-smoker, non-smoker.	1	n/a	Categorical
	Alcohol consumption	Asking participants about their alcohol consumption with answer options: Never, only at festive occasions, several times a month, once a week, several times a week, daily.	1	n/a	Categorical
	Physical activity	Asking participants about how many days a week they spend at least 30 min cycling, household activities, gardening or sports.	1	0 to 7	Continuous
Health	Comorbidities	14-item comorbidity questionnaire [34]. For partners this also includes a question about cancer.	14	0, 1–2 or ≥ 3 comorbidities	Categorical
	Fatigue	For cancer survivors: Functional Assessment of Chronic Illness – Fatigue scale (FACIT-F [35];). This 13-item questionnaire has a scoring range from 0 to 52. A higher score on this scale means less fatigue.	13	0 to 52	Continuous
		For partners: The ‘Checklist Individuele Spankracht’ (Checklist Individual Strength) that has been described in Dutch [36] and has been used on samples of workers before [37]. The scale consists of 20 items with outcome categories on a 1 to 7 scale. Summary scores (potentially using four subscales) range from 20 to 140, with higher scores indicating more fatigue.	20	20 to 140	Continuous
Employment	Main tasks	Asking participants whether they engage in a job with mainly mental, mainly physical or a combination of mental and physical tasks	1	n/a	Categorical
	Years in current position	Asking participants about how many years they have spent in the current job position regardless of current employer.	1	n/a	Continuous
	Years of paid employment	Asking participants about how many years they have spent working in general and at their current employer	1	n/a	Continuous
	Contract type	Asking participants about their contract type with four answer options: permanent contract, contract for fixed amount of time, secondment contract, contract through employment agency.	1	n/a	Categorical
	Shift work	Asking participants what sort of shifts they work in with answer options: day shifts, and shift work.	1	n/a	Dichotomous
	Company size	Asking about the size of the company with answer options 1–9, 10–99 and ≥ 100	1	n/a	Categorical
	Company sector	Asking participants about their company sector, with 13 answer options (depicting the most common occupational sectors in the Netherlands) and the answer option ‘other’	1	n/a	Categorical
	Time since first day of sick leave	Asking participants about their day of sick listing, from which the number of days between the first day of sick leave and enrolment in the study can be calculated	1	1	Continuous
	Employment status partner (if applicable)	Asking participants whether their partner has a job (full-time or part-time), with answer option yes/no	1	n/a	Dichotomous
	Caregiving leave	Asking participants whether they take caregiver leave (yes/no), and if so, for how many hours per week.	2	n/a	Dichotomous and continuous
Work	Social support from supervisor/colleagues	Two subscales of the validated Dutch version of the Job Content Questionnaire (JCQ [38];), with four items each (range 4–16).	8	4 to 16 (per subscale)	Continuous
	Job insecurity	One item (four point scale) of the Dutch Questionnaire on Perception and Judgment of Work (VBBA [39];).	1	4-point scale	Continuous
	Need for recovery	11-items (two point scale) of the VBBA [39].	11	0 to 22	Continuous
	Work accommodation	Structural changes in the job/function, and the contracted working hours, but also regarding offered and accepted accommodations, e.g., lighter work, reduced hours, modified tasks, more breaks, flexible schedule.	9	n/a	Categorical
	Impact of COVID-19 on work	Five self-established questions asking participants about the impact of COVID on their work.	5	n/a	Categorical
	Work attitude	Dutch version of the Work Involvement Scale [40]. The scale consists of six statements regarding work and working in general, that are all scored on a 7-point scale. A sample item is: ‘Having a job is very important to me.’	6	0–36	Continuous
	Self-efficacy	The Dutch version of the 12-item General Self-Efficacy scale [41] (range 12–60). A sample item is: ‘When I have decided to do something, I will definitely do it.’ The Dutch version consists of 10 items.	10	11–60	Continuous
	Work-family balance	Five questions (four point scale) from the Copenhagen Psychosocial Questionnaire (COPSOQ II [42];). A higher score indicates more work-family imbalance.	5	4-point scale	Continuous
	Work intention	One question: ‘In your estimation, what are the chances that you will be at work in 6 months?’, measured with a 10-point rating scale from 1 (no chance) to 10 (very high chance).	1	10-point scale	Continuous
	Fear of COVID-19	A Dutch translation (provided by our research group) of the fear of coronavirus-19 scale [43]. The scale consists of 7 items and is scored on a 5-point rating scale, ranging from 1 (strongly disagree) to 5 (strongly agree). A higher score indicates higher fear of COVID-19.	7	7–35	Continuous
	Expectations regarding return to work	Two questions indexing whether they have a return date in mind (yes/no), and if so, what that date is.	2	n/a	Dichotomous / continuous
Economic evaluation	Health care consumption	Asking which health care professionals were visited and which medication was taken, using the iMCQ questionnaire.	19	n/a	Continuous
	Productivity loss	Asking about productivity loss, using the iPCQ questionnaire.	Varying	n/a	Continuous
	Quality of life/utility	Asking about the quality of life, using the EQ-5D questionnaire (EuroQol-5D-5L [44])	Varying	n/a	Continuous

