### Participants and recruitment

#### RCT among cancer survivors

Cancer survivors of working age (18–63 years at time of diagnosis), with histologically confirmed cancer and a life expectancy of more than 1 year will be recruited. At study entry, eligible cancer survivors have a fixed or temporary employment contract, with at least 6 months left of their contract, and a history of paid work for at least 1 year prior to diagnosis (with ≥8 contracted working hours per week). Cancer survivors can both be at work or (partly) on sick leave when entering the study. Cancer survivors will be recruited 3–18 months post-diagnosis. The cut-off for the maximum time post-diagnosis was set at 18 months for cancer survivors to be able to complete the intervention (with a maximum duration of 6 months) before a potential work disability assessment. According to Dutch legislation, work disability assessments take place after two years of sick leave to determine whether someone is disabled for work or not and may receive work disability benefits or not. Regardless of the outcome of the work disability assessment, employers are allowed to terminate the employment contract after 2 years of sick leave. Moreover, cancer survivors will be eligible for participation in STEPS if they are, or have been, treated with at least radiotherapy and/or chemotherapy. Previous research has shown that cancer survivors who received complex treatments, i.e., chemotherapy, radiotherapy, or a combination thereof, indicated lower work ability than cancer survivors who were treated with surgery alone [22]. Cancer survivors with additional treatment modalities, besides radiotherapy and/or chemotherapy, will be eligible for participation as well.

Cancer survivors will be excluded if their treating physicians consider work unfeasible, if cancer survivors have serious cognitive or psychiatric problems, or other comorbidities that would preclude them from participating in the intervention program, and/or if cancer survivors lack basic proficiency in Dutch. Cancer survivors participating in concurrent studies or rehabilitation programs aimed at sustained employment, or cancer survivors who refuse the involvement of their employer in the STEPS intervention will also be excluded.

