#### RCT among cancer survivors

The primary outcome (i.e., working hours per week) will be assessed by asking cancer survivors about their current number of actual working hours. Hence, the primary outcome ranges from zero hours (for those on full sick leave) up to the number of working hours per week in the participant’s employment contract (for those fully returned to their work). This outcome was chosen as, according to the Dutch system, RTW is typically characterised by a gradual increase in work hours, while this measure is also important for workers trying to retain work. Secondary outcomes measures include: change in working hours (as a percentage of the contract hours at baseline), employment status (at work/not at work), sickness absence days, RRTW, work ability, health-related work functioning (only for cancer survivors who returned to work), time to RTW (only for cancer survivors who were on sick leave at baseline), and health-related quality of life. In addition to abovementioned outcome measures, information on a number of additional parameters (see Table 1 for a full overview) will be gathered, to describe the study sample, to include as potential confounder(s), and/or to conduct subgroup analyses.

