#### RCT among cancer survivors

Representativeness of participants will be evaluated by comparing cancer survivors who are included in the RCT with aggregated data of all potentially eligible cancer survivors from the NCR, using students’ t-test or appropriate non-parametric tests for the following characteristics: gender, age, time of diagnosis, tumour type and stadium and treatment. Moreover, reason of non-response at baseline (from the answer card) and during the follow-up period will be tabulated to get a better understanding of the representativeness of the study sample.

Baseline sociodemographic and clinical characteristics of the intervention group and the control group will be described and compared. Primarily, all analyses will be conducted on an intention-to-treat basis. In addition, per-protocol analyses will be carried out, in which only cancer survivors who fully complete the intervention according to protocol (i.e., having completed a minimum of three sessions: an introductory session, at least one one-on-one session with an occupational therapist, and at least one session with the reintegration consultant) will be compared to the control group.

To evaluate between-group differences on the aforementioned primary and secondary outcomes, generalized estimating equations (GEE) for longitudinal data (i.e., with the primary and secondary outcomes at six (T1) and 12 months of follow-up (T2)) will be used, adjusted for baseline values of the outcome and using appropriate tests for ordered and continuous data. This approach accounts for correlated within-subject responses, allows for non-normally distributed variables and deals adequately with missing data [46–48]. If the data are not missing completely at random, non-ignorable drop-out will be adjusted for [49]. Short- (T1) and long-term (T2) effects of the intervention will be reported separately. Effect sizes will be expressed in beta, with 95% confidence interval.

The secondary outcome ‘time to RTW’ will be analysed with time-to-event analysis [50]. A Kaplan-Meier curve will be drawn, and differences between the two groups will be tested with the log rank test. In addition, the Cox proportional hazard model of survival analysis will be applied to estimate hazard ratios and the corresponding 95% confidence intervals.

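### Time to RTW runs from the first sick day to any first work day in everyone on leave at baseline, so events and risk time before randomisation dilute this secondary comparison

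*Protocol article*

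**What the plan says.** Table 2 (Measurements) defines the duration as "the number of calendar days between the first day of sick leave and the first day of work, either fulltime or part-time", with the condition that work continues "for at least 28 consecutive days without recurrence". Table 1, footnote b, gives the population: "Only completed by participants who were on sick leave at baseline". The Measurements text for the RCT repeats that restriction.

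Eligibility (Participants and recruitment, RCT) allows a mixed population: "Cancer survivors can both be at work or (partly) on sick leave when entering the study". Recruitment is 3 to 18 months after diagnosis, and randomisation follows the baseline questionnaire.

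For the analysis (Statistical analyses, RCT), a Kaplan-Meier curve is drawn, "differences between the two groups will be tested with the log rank test", and a Cox model gives the hazard ratio. The article does not mention randomisation as time origin, delayed entry, or returns that precede baseline.

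**The concern.** Two features of the definition do not fit a randomised comparison.

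- **The event can lie in the past.** Part-time work counts as return, and someone on partial leave is already working part-time. Unless they resumed less than 28 days before baseline, or relapsed, they met the event before allocation. Treatment cannot have influenced it, yet it counts as an event in both arms.
- **The clock starts too early.** Anyone on full leave at randomisation has, by design, had no earlier return that still holds. An ordinary analysis from the first sick day nevertheless counts them as at risk for all the months before they entered.

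At stake is a real benefit on a core return-to-work outcome being reported as small or absent, with a Kaplan-Meier curve that does not describe return after allocation.

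**Working it through.** **1. The plan's own figure.** None is given for time to RTW. The sample size rests on weekly working hours: n per arm = 2 × (1.96 + 0.84)² × 13² / 5.5² ≈ 87.7, so 88, or 176 in total. With 25% attrition, 176 / 0.75 = 234.7, so 235 against the stated 236. This reproduces and does not depend on time to RTW.

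**2. Who is in the analysis set?** The eligibility sentence treats partial leave as a form of sick leave. Where the authors mean full leave they say so: the bottom of the primary scale is "zero hours (for those on full sick leave". The time-to-RTW restriction lacks that qualifier. The Measurements text also says that "RTW is typically characterised by a gradual increase in work hours", and the Economic evaluation section treats people on partial leave as productive during the hours they have resumed. Inclusion of partial leave is the better reading, though no sentence says it outright.

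**3. Assumptions not in the documents.** Entry is uniform over 3 to 18 months after the first sick day (the article gives this window from diagnosis). Follow-up is 12 months, as in the article. The return hazard in controls is constant at 0.06 or 0.10 per month, so 1 − e^(−0.72) = 51% or 1 − e^(−1.2) = 70% return within 12 months. The true hazard ratio after randomisation is 1.5. The share p already working part-time is 20, 40 or 60%.

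**4. Share of events that precede randomisation.** In the intervention arm 1 − e^(−1.08) = 66% or 1 − e^(−1.8) = 83% return, so the average r over both arms is 0.587 or 0.767. The share is p / (p + (1 − p) × r):

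- p = 20%: 0.2/0.670 = 0.30, or 0.2/0.814 = 0.25
- p = 40%: 0.4/0.752 = 0.53, or 0.4/0.860 = 0.47
- p = 60%: 0.6/0.835 = 0.72, or 0.6/0.907 = 0.66

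**5. Rough effect on the hazard ratio.** Past events carry a log hazard ratio of 0, so the estimate is roughly exp{(1 − share) × ln 1.5}, with ln 1.5 = 0.405. This gives 1.33 to 1.36, 1.21 to 1.24 and 1.12 to 1.15.

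**6. The clock.** At time t the apparent hazard ratio is the true one multiplied by f1/f0, where f is the fraction of an arm's nominal risk set that has actually been randomised. If the intervention works, its randomised members leave the risk set faster, so f1 < f0 and the ratio shrinks.

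**7. Simulated Cox estimates, both mechanisms together (true value 1.5).**

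| On partial leave | As written | From randomisation, full leave only |
|---|---|---|
| 20% | 1.28–1.34 | about 1.5 |
| 40% | 1.18–1.23 | about 1.5 |
| 60% | 1.11–1.16 | about 1.5 |
| 0% (clock alone) | 1.39–1.46 | about 1.5 |

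Delayed entry at randomisation, with past events excluded, also recovers about 1.5.

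**8. Power.** The number on leave is not given, so these sizes are assumed. The comparison is the plan as written against analysis from randomisation in those on full leave, at 20 / 40 / 60% partial.

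- 150 on leave, true hazard ratio 1.8, control hazard 0.08 per month: 56 / 34 / 18% against 79 / 65 / 49%.
- 120 on leave, true hazard ratio 2.0, half of controls returning within 12 months: 54 / 35 / 12% against 72 / 61 / 47%.

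The smaller set has the higher power in every setting.

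**9. No true effect.** With 120 or 176 on leave, the plan as written rejects in 3.5 to 6.75% of 400 replicates. The Monte Carlo standard error is √(0.05 × 0.95 / 400) = 1.1 percentage points, so this is compatible with 5%.

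**The case against.** The strongest objection concerns the population. Where the authors want partial status included they write it in brackets, as in the eligibility sentence and in Table 1, footnote c. Footnote b has no such bracket and could mean only those not yet back at work. That reading is possible but weaker, for the reasons in step 2. Even if it is right, the clock problem remains, at a smaller size.

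A reader might take the T0 mark against time to RTW in Table 1 as proof that returns before randomisation count. It is not. Every RCT work outcome carries that mark, including change in working hours, which Table 2 defines at follow-up.

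A reader might also infer that participants on partial leave tell us nothing about the effect. The 28-day rule prevents that conclusion: someone who resumed shortly before baseline, or relapsed, may not have had a qualifying event, and allocation can still affect whether the return lasts. The rule does not help with those long settled in part-time work.

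Finally, delayed entry could be left to an analysis plan that is not shown, and the variable it needs is collected. That stands in part: a correct analysis remains possible. But the article does fix the duration, the population and the methods, and these followed literally give the diluted result.

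**Conclusion.** The definition should be corrected. As written, it counts returns before randomisation as events and time before randomisation as time at risk. The result is attenuation and lost power: for a true hazard ratio of 1.5, about 1.3, 1.2 and 1.13 with 20, 40 and 60% on partial leave, or about 1.39 to 1.46 if only full leave was meant. These sizes rest on assumed entry times, hazards and shares; the documents support the direction, not a specific figure.

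A reader might infer that the trial's main conclusion is at risk, or that a false claim of benefit could follow. Neither is supported. Time to RTW is one of eight listed secondary outcomes, the primary analysis of working hours and its sample size do not use it, and type I error is preserved. The point should be fixed but does not undermine the trial.

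**What to change.** In Table 2, Table 1 footnote b and the Statistical analyses section:

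- Define the analysis set as participants who have not yet met the RTW event at T0: zero actual working hours, or a resumption not yet sustained for 28 days.
- Time from randomisation, with time since the first sick day as a covariate; or keep the sick-leave clock with delayed entry at randomisation.
- Say how a return that straddles T0 is dated. Dating every event at completion of the 28 days would place it after randomisation.
- If people on partial leave are to be included, define for them a separate event not yet reached at T0, for example sustained return to full contract hours, timed from randomisation.

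The cost is wording. Actual hours and time since the first sick day are already collected at T0. The downside is fewer participants in this secondary analysis. Because those who analyse the results are not blinded (Randomization section), the rule should be set before outcome data are examined.
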